#### 2.10.4. Effect of iDECIDE

The primary effects of interest are whether, for students assigned to the iDECIDE program after their first substance use infraction vs. students who receive standard disciplinary actions, there is (a) an increase in knowledge about substances and their impact and (b) a reduction in days spent using. Effects will be examined using a fixed effect coded as 0 at the *time-of-infraction* and for follow-up time points pre-intervention and coded as 1 at the *45-day-follow-up* and *90-day-follow-up* time points post-intervention. The primary analysis will be the interaction of this variable with a variable indicating whether the school district is in the exposed phase of the study.

We will use an intent-to-treat design. We will examine any student with a substance use infraction in the exposed phase irrespective of actual attendance in the program. Data for primary analyses will only be considered from the first infraction on record.

The study will be conducted as (a) a superiority study on the knowledge endpoint, and (b) a non-inferiority trial on the substance use endpoint. Statistical significance will be defined as a two-sided posterior *p* < 0.025. The non-inferiority margin for substance usage was determined via the fixed margin method (43). Evan-Whipp et al. (44) report results from the International Youth Development Study on what school discipline policies predict reductions in cannabis use. Two discipline approaches significantly predicted a reduction in cannabis use: lecture from teacher (OR = 0.61, 95% CI = 0.45 to 0.83) and police involvement (OR = 0.74, 95% CI = 0.55 to 1.00). The pooled results (OR = 0.68, 95% CI = 0.50 to 0.92) suggest a lower margin of 1.09. Corresponding analyses for alcohol (45) and cigarette use (46) found no significant discipline approaches that predicted reduced use after adjusting for confounders. Using a preserved effect of 50% per FDA guidelines, the minimum non-inferiority threshold based on previous literature is an odds ratio of 1.045.

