#### 2.10.5. Clinical significance

The direction and statistical significance for the difference in outcomes prior vs. after implementation of the iDECIDE program yield the following possible results for each outcome: (1) The iDECIDE program results in changes in the knowledge survey that are either (a) superior, (b) inferior, or (c) non-significant compared to standard disciplinary approaches, (2) the iDECIDE program results in reduction in substance use that is either (a) superior, (b) equivalent, (c) non-inferior, or (d) inferior compared to standard disciplinary approaches. The resulting 12 combinations of the results for the knowledge survey and substance use can be partitioned into 3 decisions regarding the clinical significance of the iDECIDE program compared to standard disciplinary approaches: (1) as or better performance, (2) worse performance, or (3) complex results (e.g., improvement in one outcome combined with worse performance on the other). Table 3 summarizes the 12 possible combinations of results and the corresponding decision about the effectiveness of the iDECIDE curriculum.

**Table 3 T3:** Pattern of significant finding and associated conclusion regarding relative effectiveness of iDECIDE vs. standard disciplinary action.

**Significant change relative to standard disciplinary actions^*^**	**Conclusion**
Substance use ▾ and knowledge score ▴	iDECIDE program is as or more effective than standard disciplinary actions.
Substance use ■ and knowledge score ▴	
Substance use ▾ and knowledge score ▴	
Substance use ▾ and knowledge score ~	
Substance use ■ and knowledge score ~	
Substance use ▾ and knowledge score ~	
Substance use ▴ and knowledge score ▾	iDECIDE program is less effective than standard disciplinary actions.
Substance use ▴ and knowledge score ~	
Substance use ▴ and knowledge score ▴	Pattern of results is complex and difficult to interpret, requiring further study.
Substance use ▾ and knowledge score ▾	
Substance use ■ and knowledge score ▾	
Substance use ▾ and knowledge score ▾	

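### Table 3 has no row for a substance-use result that shows neither non-inferiority nor inferiority, and the pooled interval behind the 1.045 margin matches averaged limits, with no pooling method or correlation stated

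*Protocol article*

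**What the plan says.** Section 2.10.4 of the protocol article makes substance use a non-inferiority endpoint and derives its margin by the fixed margin method. The inputs are two odds ratios for cannabis use, both from one report of one study: "lecture from teacher (OR = 0.61, 95% CI = 0.45 to 0.83") and "police involvement (OR = 0.74, 95% CI = 0.55 to 1.00"). It continues: "The pooled results (OR = 0.68, 95% CI = 0.50 to 0.92) suggest a lower margin of 1.09". The margin follows: "Using a preserved effect of 50% per FDA guidelines, the minimum non-inferiority threshold based on previous literature is an odds ratio of 1.045". The test level is also set there: "Statistical significance will be defined as a two-sided posterior *p* < 0.025".

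Section 2.10.5 says that iDECIDE can yield a reduction in "substance use that is either (a) superior, (b) equivalent, (c) non-inferior, or (d) inferior compared to standard disciplinary approaches". Four substance-use results times three knowledge results give 12 combinations, and Table 3 assigns each to one of three conclusions. The table's footnote defines inferiority as a statistically significant worsening, and keeps the symbol for no significant difference for the knowledge survey alone. No bounds for equivalence are given.

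**The concern.** There are two separate problems on the same endpoint.

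**The result list.** A non-inferiority test can fail without showing harm: the interval for the odds ratio may include both 1 and 1.045. Such a result is not superior, not non-inferior and, by the footnote, not inferior. Nor can it be equivalent under any upper bound at or below the margin. The article calls its 12 combinations the possible ones, yet this result is not among them. It would have to be classified after the data are known. If equivalence were read loosely as no significant difference, a failed non-inferiority test would fall among the rows concluding that iDECIDE performs at least as well.

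**The margin.** The interval described as pooled is about as wide, on the log scale, as each of the two intervals that went into it. The primary threshold therefore cannot be reproduced from the derivation given, and the stated 50% preservation does not follow from it.

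**Working it through.** **A. Reproducing the margin (section 2.10.4)**

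Plain averages of the two printed results:
- estimate: (0.61 + 0.74)/2 = 0.675, prints as 0.68
- lower limit: (0.45 + 0.55)/2 = 0.500, prints as 0.50
- upper limit: (0.83 + 1.00)/2 = 0.915, prints as 0.92

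All three match. Then 1/0.92 = 1.087, prints as 1.09, and 1 + 0.09/2 = 1.045.

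Precision, with SE = ln(upper/lower)/(2 × 1.96):
- teacher lecture: ln(0.83/0.45)/3.92 = 0.1562
- police involvement: ln(1.00/0.55)/3.92 = 0.1525
- stated pooled result: ln(0.92/0.50)/3.92 = 0.156, so no gain

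**B. Inverse-variance pooling on the log scale**

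The weights 1/SE² give shares of about 0.488 and 0.512. The pooled log odds ratio is 0.488 × (−0.4943) + 0.512 × (−0.3011) = −0.395, so OR 0.673. With independent estimates SE = 0.109 and the interval is 0.544 to 0.834. Heterogeneity is small (Q = 0.78 on 1 df), so a DerSimonian-Laird analysis gives the same result.

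Both odds ratios come from one study and their correlation ρ is not given, so the range is shown. M1 is the inverse of the upper limit, M2 = √M1, and the share preserved by 1.045 is 1 − ln(1.045)/ln(M1).

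| ρ | Pooled 95% CI | M1 | M2 | Share preserved by 1.045 |
|---|---|---|---|---|
| 0 | 0.54 to 0.83 | 1.199 | 1.095 | 76% |
| 0.5 | 0.52 to 0.88 | 1.143 | 1.069 | 67% |
| 1 | 0.50 to 0.91 | 1.097 | 1.048 | 53% |

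Only correlations near 1 approach the stated interval.

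**C. How often no row applies**

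The SE of the trial's log odds ratio is not in the document. It is assumed here, back-solved from section 2.10.12: power 0.82 for 7 waves, ratio 1 against 0.8, SE = effect/(z for alpha + 0.915).
- effect 0.2: 0.2/(2.241 + 0.915) = 0.063 at two-sided 0.025; 0.2/(1.960 + 0.915) = 0.070 at 0.05
- effect −ln 0.8 = 0.223: 0.071 and 0.078 respectively

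This treats the ratio scale as if it were the log-odds-ratio scale.

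With true OR 1 and a normal approximation at two-sided 0.025, P(non-inferior) = Φ(ln(margin)/SE − 2.241), which includes superiority. P(inferior) = 0.0125. The remainder has no row.
- Margin 1.045, SE 0.0634: Φ(0.0440/0.0634 − 2.241) = 0.061; remainder 1 − 0.061 − 0.0125 = 0.927
- Margin 1.045, SE 0.0776: Φ(0.567 − 2.241) = 0.047; remainder 0.940
- Margin 1.095, SE 0.0634: P(non-inferior) = 0.209; remainder 0.778
- Margin 1.095, SE 0.0776: P(non-inferior) = 0.142; remainder 0.846

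Testing at two-sided 0.05 with margin 1.045 leaves 87-89% without a row. At two-sided 0.025 the share exceeds one half whenever the SE is above about 0.020. It rises with the SE: about 95% at 0.10 and 97% at 0.20.

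**The case against.** The strongest reply is that the margin is conservative. A stricter margin cannot create a false non-inferiority claim, and the trial is already enrolling. The two approaches were chosen because they were significant for cannabis, while none was found for alcohol or cigarettes, which also argues against loosening the margin. This stands.

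The article does not name its pooling method, so averaging is an inference from a three-number match. Pooling with correlation 1, using unrounded inputs that would print as the published ones, can reach 0.677 (0.503 to 0.916), which also prints as stated. That too stands, but it needs an assumption the article does not state.

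A reader might infer more than the document supports:
- That half the effect was wrongly taken on the odds-ratio scale. From the averaged limit, 1/0.915 = 1.093 and √1.093 = 1.045, so log-scale halving gives the printed figures too.
- That a pooled estimate must be more precise than each input, that 1.095 is the correct margin, or that 1.045 preserves 76%. The first fails at correlation 1. The other two hold only under independence, which estimates from a single study do not guarantee.
- That the equivalence rows can never be reached. This needs bounds the article does not give.

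On the result list, Table 3's symbols are degraded in the available text, but the gap follows from the prose and footnote alone. The bounds for equivalence might stand in an analysis plan not shown. The missing class is different, because the article itself presents the list as complete. The probabilities do rest on an assumed scale. An SE larger than assumed would strengthen the point, and one small enough to overturn it would have to be below about 0.020, under a third of the lowest value used.

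**Conclusion.** Both points hold in limited form.

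The gap in the decision rule is the more consequential. Under equal effects about 93-94% of trials would end with a substance-use result that Table 3 does not cover, given the SE assumption in C. Changing the margin alone does not cure this: at 1.095 the share is still about 78-85%.

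The margin's derivation is misdescribed. The printed interval matches arithmetic averaging and fits pooling only with a correlation near 1. Depending on that correlation, half-preservation gives a margin between about 1.05 and 1.10, and 1.045 preserves about 53% to 76% of the effect instead of a derived 50%. The error is on the strict side. Its cost is a smaller chance of showing non-inferiority and a threshold readers cannot reproduce, with no added risk of a false claim.

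**What to change.** Before the analyst blind described in section 2.6 is lifted:

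1. Add a fifth substance-use result to section 2.10.5: inconclusive, non-inferiority not shown. Give it three Table 3 rows, one per knowledge result, none leading to the conclusion that iDECIDE is at least as effective. The 12 combinations become 15.
2. State the bounds for equivalence, or delete that class and its rows.
3. In section 2.10.4, state the pooling method and the correlation assumed between the two odds ratios, and correct the pooled interval accordingly.
4. Then either keep 1.045, described as a deliberately strict margin with the share of the effect it preserves, or restate M1 and M2 from the corrected interval. Keeping 1.045 is the simpler course, since it does not loosen a primary threshold during enrolment.

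The cost is wording, one recomputed interval and three table rows. No new data are needed.

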#### 2.10.5. Clinical significance

The direction and statistical significance for the difference in outcomes prior vs. after implementation of the iDECIDE program yield the following possible results for each outcome: (1) The iDECIDE program results in changes in the knowledge survey that are either (a) superior, (b) inferior, or (c) non-significant compared to standard disciplinary approaches, (2) the iDECIDE program results in reduction in substance use that is either (a) superior, (b) equivalent, (c) non-inferior, or (d) inferior compared to standard disciplinary approaches. The resulting 12 combinations of the results for the knowledge survey and substance use can be partitioned into 3 decisions regarding the clinical significance of the iDECIDE program compared to standard disciplinary approaches: (1) as or better performance, (2) worse performance, or (3) complex results (e.g., improvement in one outcome combined with worse performance on the other). Table 3 summarizes the 12 possible combinations of results and the corresponding decision about the effectiveness of the iDECIDE curriculum.

**Table 3 T3:** Pattern of significant finding and associated conclusion regarding relative effectiveness of iDECIDE vs. standard disciplinary action.

**Significant change relative to standard disciplinary actions^*^**	**Conclusion**
Substance use ▾ and knowledge score ▴	iDECIDE program is as or more effective than standard disciplinary actions.
Substance use ■ and knowledge score ▴	
Substance use ▾ and knowledge score ▴	
Substance use ▾ and knowledge score ~	
Substance use ■ and knowledge score ~	
Substance use ▾ and knowledge score ~	
Substance use ▴ and knowledge score ▾	iDECIDE program is less effective than standard disciplinary actions.
Substance use ▴ and knowledge score ~	
Substance use ▴ and knowledge score ▴	Pattern of results is complex and difficult to interpret, requiring further study.
Substance use ▾ and knowledge score ▾	
Substance use ■ and knowledge score ▾	
Substance use ▾ and knowledge score ▾	

* Statistical significance defined as p < 0.025 for a two-tailed test; The ▾ and ▴ symbols indicate a significant improvement in knowledge/drug use relative to standard disciplinary action (Superiority), the ▾ and ▴ symbols indicate a significant decrement relative to standard disciplinary action (Inferiority), and the ■ and ▾ symbols indicate equivalence and non-inferiority, respectively, relative to standard disciplinary action (specific to substance use), and the ~ symbol indicates no statistically significant difference (p > 0.025) between the iDECIDE program and standard disciplinary action (specific to the knowledge survey).

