### 2.10. Data analysis

#### 2.10.1. Overarching statistical model

The two primary outcomes will be assessed at three time points: (1) immediately after a student is first caught for a substance use infraction (i.e., baseline, *time-of-infraction*); (2) 45 days after the date of the first infraction (i.e., *45 day-follow-up*); (3) 90 days after the date of the first infraction (i.e., *90 day-follow-up*). The proposed primary outcomes (items correct on a knowledge survey and number of days out of 14 spent using a preferred substance) are both bounded counts variables. We therefore will assume (a) whether an item is correct on the knowledge survey follows a Bernoulli distribution and the number of days out of 14 spent using a substance follows a binomial distribution, and (b) these distributions (both the binomial and Bernoulli) are governed by a latent probability parameter. This latent probability describes either the likelihood of getting an item correct on the knowledge survey or the average number of days spent using a preferred substance out of 14, and the log-odds for a student's latent probability at the three assessment time points is described following a trivariate normal distribution. This statistical model will allow us to examine changes in substance use and knowledge about substances while controlling for (1) measurement error, and (2) correlations between repeated measures collected over the three time points. The means for the log-odds of the latent probabilities can be further decomposed into a summation of population-level, school-level, and student-level effects. The specific decomposition of the means for the log-odds will depend on the outcome measure.

The complexity of the statistical models (e.g., a multivariate latent measure model with both fixed and random effects and with observed data distributed as counts) is most easily handled within a Bayesian framework. However, prior distributions will need to be defined for model parameters. A conservative approach will be taken using only weakly informative priors with a diffuse range (for example, standard deviations for log-odds will be set to 2.5, estimates for fixed effects will be centered at 0, and we will use empirical Bayes priors for intercepts).

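### Table 3 never requires knowledge superiority for its favourable verdict: with a favourable substance-use result, a non-significant knowledge result earns the same conclusion as a proven gain

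*Protocol article*

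**What the plan says.** Section 2.10.1 names two primary outcomes, knowledge of drug effects and frequency of substance use: "The two primary outcomes will be assessed at three time points". Section 2.10.4 assigns the hypothesis types: "a) a superiority study on the knowledge endpoint, and (b) a non-inferiority trial on the substance use endpoint". A margin is derived for substance use alone: "the minimum non-inferiority threshold based on previous literature is an odds ratio of 1.045". The article gives no equivalence or non-inferiority margin for knowledge.

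Section 2.10.5 sorts knowledge into three results (superior, inferior, non-significant) and substance use into four (superior, equivalent, non-inferior, inferior). Table 3 maps the 12 combinations to three conclusions. Its footnote fixes the level, "Statistical significance defined as p < 0.025 for a two-tailed test", and states that the ~ "symbol indicates no statistically significant difference (p > 0.025) between the iDECIDE program and standard disciplinary action (specific to the knowledge survey"). The first six rows carry the conclusion "iDECIDE program is as or more effective than standard disciplinary actions". Three of them end in ~, including rows of the form "Substance use ▾ and knowledge score" followed by ~.

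**The concern.** The hypothesis type and the decision rule do not match. A superiority endpoint is met when superiority is shown. In the favourable block of Table 3, meeting or missing that objective makes no difference to the conclusion.

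The document also treats its two primary endpoints differently. For substance use, being no worse has to be demonstrated against a margin. For knowledge, a difference that merely fails to reach significance is allowed to stand towards an overall statement of parity. The ~ category holds estimates in the wrong direction and wide, uninformative intervals alike, so a less precise knowledge analysis makes it easier to stay in the favourable block.

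At stake is the headline. The Discussion part of the abstract expects consequences for policy, and a policy reader given only the conclusion could not tell a demonstrated knowledge gain from a failed superiority test.

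**Working it through.** **Inputs.** Two primary outcomes (2.10.1); knowledge as superiority, substance use as non-inferiority with threshold OR 1.045 (2.10.4); three knowledge and four substance-use results (2.10.5); two-sided level 0.025 (2.10.4 and Table 3 footnote).

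**Step 1. Reproduce the table's structure.** 4 × 3 = 12 combinations, as stated. Reading the rows gives 6 favourable, 2 less effective and 4 complex:

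| Substance use | Knowledge superior | Knowledge ~ | Knowledge inferior |
|---|---|---|---|
| Superior | favourable | favourable | complex |
| Equivalent | favourable | favourable | complex |
| Non-inferior | favourable | favourable | complex |
| Inferior | complex | less effective | less effective |

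The available text does not preserve the styling that separates the superior and non-inferior substance-use symbols. The reading does not depend on it, because both fall in the same block and ~ is intact.

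**Step 2. Does knowledge superiority matter to the favourable verdict?** In the first three lines the first two columns are identical, so superiority is never needed. Three of the six favourable cells rest on ~. Only the third column withholds the verdict.

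**Step 3. Illustrate how weak that condition is.** Treat the knowledge estimate divided by its standard error as normal with mean d. This is an approximation to the Bayesian analysis, reasonable given the weakly informative priors in 2.10.1. The critical value is z(1 − 0.025/2) = 2.2414. Knowledge does not block the favourable verdict unless it is significantly worse:

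P(not significantly worse) = 1 − Φ(−2.2414 − d) = Φ(2.2414 + d)

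- d = 0: Φ(2.2414) = 0.9875
- d = −1: Φ(1.2414) = 0.893
- d = −2: Φ(0.2414) = 0.595

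For comparison, P(knowledge superior) at d = 0 is 0.0125.

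**Step 4. Put it beside the substance-use condition.** The documents give no power for knowledge and no probability of reaching non-inferiority on use, so this step is an assumed scenario: independent endpoints and an 80% chance that use is at least non-inferior. The second column is the chance of the favourable verdict as the table stands; the third is the chance of reaching a row with knowledge superior.

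| Knowledge scenario | Table 3 as written | Knowledge superior as well |
|---|---|---|
| No true effect | 0.80 × 0.9875 = 0.79 | 0.80 × 0.0125 = 0.01 |
| 50% power | 0.80 | 0.80 × 0.50 = 0.40 |
| 80% power | 0.80 | 0.80 × 0.80 = 0.64 |
| 90% power | 0.80 | 0.80 × 0.90 = 0.72 |

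The middle column hardly moves with the true knowledge effect.

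**The case against.** The strongest defence is that Table 3 follows one coherent rule. Substance use sets the verdict, ~ leaves it unchanged, and a significant knowledge result in the opposite direction makes it complex. The label is a parity-type summary that does not literally claim a knowledge gain, and each knowledge result keeps its own row, so a failed superiority test stays visible to anyone who reads the left-hand column. Relabelling the favourable ~ rows while leaving the inferior-use ~ row alone would break the symmetry.

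Much of this is fair, but it does not remove the problem. A parity label still asserts that the programme is at least as good, and with knowledge at ~ nothing in the rule establishes that for knowledge. The asymmetry is justified: the less-effective verdict with ~ rests on demonstrated inferiority in use and needs no parity on knowledge. The objection does have force where substance use is superior and knowledge is ~, since a reduction in use has been shown there. The problem is sharpest in the equivalent and non-inferior ~ rows.

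Three stronger readings are tempting and are not supported:

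- A reader might infer that knowledge cannot affect the verdict unless it significantly worsens. With substance use inferior, superior knowledge moves the verdict from less effective to complex, and worsening changes nothing.
- A reader might infer that knowledge is in effect untested. Section 2.10.4 does specify a superiority test; its success simply does not count towards the favourable conclusion.
- A reader might take 98.75% as the chance of the favourable verdict, or 2 standard errors as a sizeable loss. The figure is marginal to knowledge (1 − 0.0125), and the article gives no standard error or item count with which to turn standard errors into items correct.

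**Conclusion.** The point holds in this form: knowledge is a primary endpoint declared as superiority, without a margin, yet its superiority is never needed for the favourable verdict. Given a favourable substance-use result, ~ and a proven gain lead to the same conclusion, and only significant worsening withholds it. Following the rule as written can therefore yield a statement of parity that the knowledge data do not support.

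The structural finding rests only on the published rows and footnote. The probabilities (98.75%, about 89% and about 60%) rest on a normal approximation, describe the knowledge component alone and serve as illustration. The 0.79 against 0.01 contrast further assumes independence and an 80% chance of a favourable use result.

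This should be corrected. It is not a matter left to an unseen analysis plan, because Table 3 is a complete rule for all 12 combinations. The objection lies in what it fixes.

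**What to change.** Change the conclusion column for three rows of Table 3:

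- Knowledge superior with use superior, equivalent or non-inferior: keep the present unqualified conclusion.
- Use equivalent, knowledge ~: equivalent on substance use; knowledge benefit not shown.
- Use non-inferior, knowledge ~: non-inferior on substance use; knowledge benefit not shown.
- Use superior, knowledge ~: superior on substance use; knowledge benefit not shown.
- All other rows: unchanged.

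Report the knowledge interval with each of the three ~ conclusions. Unqualified favourable cells fall from 6 to 3 of 12.

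The change needs no new data or analysis. Section 3 reports the trial as still recruiting, and section 2.6 keeps the analyst blinded until models are settled, so it can be made without sight of results if done before unblinding. The price is a less favourable headline if knowledge does not improve.
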